# A randomised controlled trial of a personalised lifestyle coaching application in modifying periconceptional behaviours in women suffering from reproductive failures (iPLAN trial)

**DOI:** 10.1186/s12905-018-0689-7

**Published:** 2018-12-04

**Keywords:** Periconceptional health, Lifestyle, Online application, Smartphone application, Coaching, Randomised control trial

## Abstract

**Background:**

Lifestyle, in particular obesity and smoking has significant impacts on fertility and an important focus for the treatment of reproductive failures is the optimisation of periconceptional lifestyle behaviours. The preimplantation intrauterine environment within the uterus is also key for embryo development and early programming. Although the benefits a healthy periconceptional lifestyle are well described, there remains a paucity of data demonstrating the efficacy of interventions designed to optimise preconceptional lifestyle behaviours and choices.

**Methods:**

This study is a prospective randomised controlled trial which aims to address the question of whether an online personalised lifestyle coaching application is an effective means of delivering periconceptional advice in women suffering from reproductive failures. Women suffering from subfertility or recurrent miscarriages attending the outpatient clinic will be randomised into either the intervention arm (personalised online lifestyle coaching application) or the control arm (standard periconceptional advice including information from NHS websites). Both groups will be asked to complete a validated lifestyle questionnaire at baseline, and 6, 12, 18 and 24 weeks after randomisation. The primary outcome is the composite dietary and lifestyle risk score at 12 weeks. The secondary outcomes will include compliance with the program, proportion achieving spontaneous conception during the study period and the dietary and lifestyle risk score at 24 weeks.

**Discussion:**

With this study, we aim to clarify whether a personalised online based lifestyle coaching application is more effective at improving behaviours than standard advice offered by National Health Service (NHS) resources. A personalised lifestyle coaching application may represent an empowering and cost effective means of delivering periconceptional advice in women with subfertility or recurrent miscarriages.

**Trial registration:**

The iPLAN trial was retrospectively registered (ISRCTN 89523555).

**Electronic supplementary material:**

The online version of this article (10.1186/s12905-018-0689-7) contains supplementary material, which is available to authorized users.

## Background

The impact of lifestyle, and in particular obesity and smoking on fertility has been well described, and optimizing preconceptional lifestyle behaviours has become a primary strategy in the treatment of subfertility, recurrent pregnancy losses, and in particular the management of anovulation secondary to polycystic ovary syndrome [1]. It is also becoming clear that the preimplantation intrauterine environment is a key determinant of embryo development and early programming, and recent work has shown that the nutritional content of endometrial secretions is directly affected by diet [2].

The periconceptional period during which external and environmental factors exert significant influence on gamete and embryo health is considered to extend from 14 weeks pre-conception to 10 weeks gestation [3]. Factors shown to affect fertility and the chances of a healthy live birth include weight, diet, intake of vitamins, iodine and alcohol, smoking, substance abuse, environmental pollutants, infections, medical conditions, medications and family medical history [4]. Many important modifiable factors in the preconception period have also been shown to have important effects on the developing fetus [5, 6] with longer term impacts on the health of the offspring [7]. The detrimental effects of tobacco smoking have been well established [8, 9]; maternal tobacco smoking has been associated with subfertility, congenital malformations and deleterious effects on fetal and infant growth [10–12]. Nutrition is another modifiable factor; the occurrence of neural tube defects and altered fetal growth trajectories has been linked to deficiencies in folate, an essential vitamin B [13] and all woman planning a pregnancy are recommended 0.4 to 0.5 mg of folic acid per day for prevention of neural tube defects [14]. A ‘Mediterranean diet’ or a diet high in vegetable oils, fish and legumes and low in carbohydrate rich snacks in IVF patients have been shown to have positive effects on the level of red blood cell folate and vitamin B6 in the blood and follicular fluid, as well as increases the chances of pregnancy [15].

While there is a widespread recognition of the impact of preconceptional health on fertility outcomes and long term effects for the offspring, there is paucity of data demonstrating the efficacy of interventions designed to optimise preconceptional lifestyle behaviours and choices. One study has shown that tailored preconception counselling on lifestyle behaviours in subfertile couples in the outpatient tertiary clinic seems to reduce, in the short term, prevalence of harmful behaviours [16]. The NHS has a website which provides general information and advice for women planning a pregnancy [17]. For clinicians, there is general guidance offered by the National Institute of Health and care Excellence (NICE) on preconception advice and management [18]. The optimal method for delivering preconceptional lifestyle advice remains unclear. The use of personal or group lifestyle coaching can be costly and demanding, and there may be problems with non-compliance.

Recently, a novel online smartphone application delivering lifestyle coaching system has been developed, which may offer effective, low burden and low cost method of delivering peri-conceptional lifestyle advice. The ‘Smarter Pregnancy’ application addresses current priorities in the NHS; the NHS Five Year forward View, published in October 2014 argues for initiatives to empower patients and communities to take control of their health in order to help moderate rising demand on the NHS [19]. This online smartphone application may enable woman to be more in control of their health before and during pregnancy and may assist them in making lifestyle choices.

Whilst this online lifestyle application has been piloted, studies have only focussed on women in the primary care setting (University College London group [20]) and women and men who are generally seeking to become pregnant within 6 months (Rotterdam Group [21]). The effectiveness of the smartphone application in changing lifestyle choices has not been studied specifically in women with subfertility or in those suffering from recurrent miscarriages. Providing advice about factors affecting fertility and pregnancy outcomes in these women is a crucial step in helping them make lifestyle modifications to increase their chances of timely conception and chances of delivering a healthy, live baby.

## Methods and design

### Study objective

The prospective randomised controlled trial (the iPLAN trial ‘Impact of a Personalised Lifestyle coaching phone ApplicatioN in modifying peri-conceptional behaviours) aims to address the question of whether an online based lifestyle coaching application is an effective means of delivering periconceptional advice in women suffering from reproductive failures.

### Hypothesis

The hypothesis being tested in this study is that a smartphone based online lifestyle coaching application will be a more effective means of modulating periconceptional lifestyle behaviours compared to conventional measures of periconceptional counselling through standard information provided by NHS websites and patient information leaflets.

### Study population and recruitment

All women who attend the outpatient department in Princess Anne Hospital, Southampton and Salisbury District Hospital who meet the inclusion and exclusion criteria will be invited to participate in the iPLAN study. Women participating in the iPLAN trial will be women suffering from subfertility or recurrent miscarriages, aged between 18 and 45 years and actively trying to conceive. They will also need to be fluent in the use and understanding of English, and have a smartphone capable of running the online application.

Exclusion criteria include women who are on a specific diet for medical reasons, women with insulin diabetes and those undergoing any other means of lifestyle coaching, for example personal trainer or group lifestyle coaching.

Eligible patients will be informed about the iPLAN study during their first outpatient appointment and consultation with the medical team. In addition, patients can self-refer by contacting the research team, the details of which are on recruitment posters displayed in the outpatient departments of the participating hospitals. Eligible patients who wish to participate will need to provide written consent. After this, the patient will be given a unique activation code to the online lifestyle coaching application. Once registered, participants will be randomised by the application.

### Study design

This study is a two-centre randomised control trial of using an online smartphone application in providing lifestyle coaching and modifying lifestyle parameters in women attending the outpatient department in Princess Anne Hospital, Southampton and Salisbury District Hospital. A flow diagram of the study design is shown in Fig. 1. Participants seen in the outpatient clinic suffering from infertility or recurrent miscarriages, who may be suitable for the study will be referred by the clinician to the research nurse. The research nurse will explain in detail about the study, ensure that the inclusion and exclusion criteria are met and takes informed written consent.

**Fig. 1 Fig1:**
[figure not shown]
Flow diagram for the iPLAN study design

Women from both intervention and control group will be asked to visit the ‘Smarter Pregnancy’ website (www.smarterpregnancy.org.uk) and will be asked to register and activate their account by a unique validation code. Women will be asked to complete a baseline lifestyle questionnaire which assesses parameters including smoking habits, alcohol consumption, diet, exercise and weight, and then will be randomised by the ‘Smarter Pregnancy’ computer programme to either intervention arm or control arm. Both intervention and control group login to ‘Smarter Pregnancy’ using their personalised credentials created at registration.

In the intervention arm, women will have access to a personalised smartphone lifestyle coaching program. Through baseline and follow up lifestyle questionnaires (at 6, 12, 18 and 24 weeks) sent out via email, tailored lifestyle advice is generated; emails with tips, facts and recipes are sent to the intervention arm participants to encourage them to change unhealthy habits and maintain healthy habits. Coaching is focussed on study subjects who report inadequate intake of vegetables and fruit, and absence of folic acid supplementation, and those with unfavourable alcohol and smoking habits, which are identified by the baseline and follow up questionnaires. The smartphone application allows the women to update their pregnancy status; if the subject is pregnant, lifestyle advice is adapted for the pregnancy. Those randomised to the control arm will have access to standard periconceptional advice, including information from NHS websites.

The results will be analysed to determine whether a smartphone lifestyle coaching application can improve lifestyle behaviours in the periconceptional period, through a validated lifestyle questionnaire (see Appendix 1) at 6, 12, 18 and 24 weeks after randomisation. Patient compliance with the system at specific time points (at 6, 12, 18 and 24 weeks after randomisation) and the proportion of women achieving spontaneous conception during the study period will also be assessed. The expected length of time each subject will participate in the study for is 6 months after randomisation.

### Primary and secondary endpoints

The primary endpoint of the study is the composite dietary and lifestyle risk score at 12 weeks after randomisation. Secondary endpoints include (i) percentage of patients remaining compliant with system at 12, 18 and 24 weeks after randomisation, (ii) proportion achieving spontaneous conception during study period and (iii) composite dietary and lifestyle risk score at 24 weeks after randomisation.

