### Statistical analysis

#### Sample size calculation and power considerations

In order to show a difference in the proportion of participants achieving a high composite lifestyle score from 30% in the control arm to 50% in the study arm after 24 weeks of the intervention, with 80% power at a *P* value of < 0.05, 93 patients will be required in each arm. We have assumed a randomisation rate of 50% and assuming a drop-out rate of 15–20%, 220 patients will be randomized to each arm (440 patients to be recruited in total).

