#### Data analysis

The difference between two groups for the composite score will be expressed as a proportion of those achieving high scores at the end of the intervention period. Chi squared testing will be applied to test these categorical variables for significance. Differences in parameters will be tested by a two-tail Mann Whitney U test. In order to adjust for predefined confounders such as age, socioeconomic class, educational attainment, working status and ethnicity, multiple regression analysis will be performed.

Missing data will be described, for example, by presenting the number and percentage of individuals in the missing category. All data collected on collection forms will be used, since only essential data items will be collected. No data will be considered spurious in the analysis since all data will be checked and cleaned before analysis. Range checks, identification of extreme values (Mean +/− 3*Std Dev) and consistency checks will be used to identify possible data errors.

An intention to treat analysis will be performed. No interim analysis is planned.

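### The primary endpoint is set at 12 weeks, but the sample size is set at 24 weeks and the only stated composite-score comparison reads as 24 weeks, so the 80% power does not apply to the declared primary endpoint

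*Protocol article*

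**What the plan says.** All references are to the protocol article.

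- **Abstract, Methods:** "The primary outcome is the composite dietary and lifestyle risk score at 12 weeks".
- **Primary and secondary endpoints:** "The primary endpoint of the study is the composite dietary and lifestyle risk score at 12 weeks after randomisation". The last item in the list of secondary endpoints is "iii) composite dietary and lifestyle risk score at 24 weeks after randomisation".
- **Sample size calculation and power considerations:** the trial is sized on the proportion of participants with a high composite score, "from 30% in the control arm to 50% in the study arm after 24 weeks of the intervention", at 80% power and a significance level of 0.05, giving "93 patients will be required in each arm". The same paragraph assumes a 50% randomisation rate and 15–20% drop-out, and gives 220 randomised per arm, 440 in total.
- **Data analysis:** the group difference in the composite score "will be expressed as a proportion of those achieving high scores at the end of the intervention period", tested by chi-squared. A two-tailed Mann-Whitney U test is named for unspecified parameters, and multiple regression for adjustment. Neither carries a time point.
- **Study design:** questionnaires, and the tailored advice built on them, run at 6, 12, 18 and 24 weeks. Participation lasts about 6 months.

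**The concern.** The two places that define the primary endpoint agree on week 12. The two that say how the trial is sized and how the composite score is compared point to week 24. A reader cannot tell which result is meant to decide the trial.

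Two things are at stake. First, the stated power is a claim about the 24-week contrast. It carries over to week 12 only if the same contrast already holds halfway through the coaching, and the article does not say that it does. Second, both time points will be available at analysis and each can be defended from the published text, so the choice could be made, or seem to have been made, after the results are known. The article states that the trial was registered retrospectively, which makes a clear published statement of the primary time point more valuable.

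**Working it through.** **1. Time points side by side**

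| Section | Variable | Time point | Status |
|---|---|---|---|
| Abstract, Methods | composite risk score | 12 weeks | primary |
| Primary and secondary endpoints | composite risk score | 12 weeks | primary |
| Primary and secondary endpoints | composite risk score | 24 weeks | secondary (iii) |
| Sample size | proportion with a high score | 24 weeks | basis for N |
| Data analysis | proportion with a high score | end of intervention period | only stated composite comparison |

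The end of the intervention period reads as 24 weeks, because the sample-size paragraph describes the intervention as lasting 24 weeks and Study design runs coaching questionnaires to week 24. No section gives a 12-week effect, a 12-week power or a 12-week composite comparison. The form of the endpoint also changes, from a score to a proportion above an unnamed cut.

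**2. Reproducing the stated sample size**

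Inputs from the sample-size section: p1 = 0.30, p2 = 0.50, power 0.80, alpha 0.05 (sidedness not stated there; two-sided reproduces the figure). Mean proportion p̄ = 0.40.

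n per arm = [1.960·√(2p̄(1−p̄)) + 0.8416·√(p1(1−p1) + p2(1−p2))]² / (p2−p1)²

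= [1.960·√0.48 + 0.8416·√0.46]² / 0.04 = (1.358 + 0.571)² / 0.04 = 93.

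This matches exactly, with pooled variance and no continuity correction. The arithmetic is sound, but it belongs to the 24-week contrast.

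**3. Power at 12 weeks under assumed effects**

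The article gives no 12-week rates, so the values below are assumptions, with control held at 30%.

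Power = Φ{ [(p2−p1)√n − 1.960·√(2p̄(1−p̄))] / √(p1(1−p1) + p2(1−p2)) }

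Example, 30% vs 45%, n = 93: (1.4465 − 1.3419) / 0.6764 = 0.155, and Φ(0.155) = 0.56.

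Two bases for n are shown: the 93 evaluable per arm that the article requires, and 220 randomised per arm less drop-out (220 × 0.80 = 176; 220 × 0.85 = 187).

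| Assumed 12-week rates | n needed for 80% | Power, n = 93 | Power, n = 176 | Power, n = 187 |
|---|---|---|---|---|
| 30% vs 50% | 93 | 80% | 97% | 98% |
| 30% vs 45% | 163 | 56% | 83% | 85% |
| 30% vs 40% | 356 | 30% | 50% | 53% |

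The 50% randomisation rate makes the 220 ambiguous. If 440 is the number before that rate is applied, 440 × 0.5 × 0.85 / 2 = 93.5 evaluable per arm (88 at 20% drop-out), which is close to the n = 93 column. That is a separate question and is not settled here, so both bases are shown.

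**4. Type I error if either time point could be claimed**

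With two two-sided 0.05 tests whose statistics are bivariate normal with correlation ρ, the error is 1 − P(|Z1| < 1.96 and |Z2| < 1.96).

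| Assumed ρ | 0.5 | 0.6 | 0.7 | 0.8 |
|---|---|---|---|---|
| P(either significant) | 9.1% | 8.8% | 8.3% | 7.8% |

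These figures hold only under a rule that success at either time point suffices.

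**The case against.** The strongest reply has four parts.

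*A test for week 12 may be there.* The primary endpoint is a score, a rank test suits a score, and a Mann-Whitney test is named. Tying tests to visits is also often left to an analysis plan that is not shown. This stands in part: it would be too strong to say that week 12 has no possible test. What can be said is that none is expressly linked to it, while the one comparison named for the composite score is placed elsewhere.

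*The Data analysis section does not say 24 weeks and labels no test as primary.* That is correct. The 24-week reading comes from taking it together with the sample-size and Study design sections. It is the natural reading, but it is an inference.

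*The type I error is not inflated by anything written.* A reader might infer that the plan runs at 8–9%. The documents do not support that: no section allows success at either time point, and the abstract and endpoint section agree that week 12 is primary. The figure measures what loose wording could permit, under assumed correlations.

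*Underpowering is not demonstrated.* A reader might also infer a trial that is too small. The 12-week effect is unknown. If it is 30% vs 50%, 93 per arm still gives 80%, and 220 randomised per arm would give at least 83% even at 30% vs 45%.

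None of this removes the conflict between the 12-week endpoint and the 24-week sample size. Both are explicit in the current text, so condensation into an article does not explain it, and an analysis plan that chose one would still contradict part of this protocol.

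**Conclusion.** The contradiction holds and should be corrected. The primary endpoint is declared at week 12. The sample size is set at week 24, and the only stated composite-score comparison reads as week 24, a time point listed as secondary. The 80% power statement therefore does not apply to the declared primary endpoint, and no test is expressly tied to week 12.

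The consequence for power cannot be fixed from the documents. Over assumed 12-week contrasts of 30% vs 50% down to 30% vs 40%, power runs from 80% to 30% with 93 evaluable per arm, and from about 97–98% to 50–53% with 176–187. The type I error of about 8–9% is a conditional risk, at assumed correlations of 0.5–0.8 and only if either time point were allowed to count. The point rests on the contradiction itself and not on a demonstrated loss of power or an established error rate.

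**What to change.** Before unblinding, choose one primary time point and one endpoint form, and use them throughout. If week 12 stays primary:

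1. In Data analysis, state that the primary comparison is at 12 weeks.
2. In the sample-size section, give a justified 12-week effect and the power that results. Relabelling 30% vs 50% as a 12-week effect would not be enough, since nothing in the article supports it at that time.
3. Say whether the primary variable is the score or the proportion with a high score, and name the test that matches.
4. Keep the 24-week result as secondary and report it only as such.

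The cost is a short wording amendment to the sample-size, data-analysis and endpoint text, plus the work of justifying a 12-week effect. No new data are needed, because questionnaires are already scheduled at both 12 and 24 weeks.

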### Participating hospitals

This is a two centre study that will be conducted in the outpatient departments of the Princess Anne Hospital, Southampton and Salisbury District Hospital. These are part of the University Hospital Southampton NHS Foundation Trust and Salisbury NHS Foundation Trust respectively.

### Randomisation

Participating women will be randomised in program by the computer generation of a series of validation codes which is unique for each participant. After completion of the baseline questionnaires, women will be randomised to the intervention or the control group. The randomisation process will be concealed and the research team will be blinded to the randomisation.

### Data collection

All women giving informed consent will be asked to complete an electronic registration and baseline questionnaire using their computer, laptop, tablet or smartphone. The validated lifestyle questionnaire is done at baseline, at 6, 12, 18 and 24 weeks after randomisation. Subjects will be sent an email with a link to the questionnaire at the time points specified. The lifestyle questionnaire includes assessment of folate and vitamin D intake, pregnancy status, BMI, diet (including fruit, vegetables, meat and/or meat substitutes, liver and/or liver products, shellfish and fish products, savoury snacks, sweet snacks, bread and rice, and ready-made meals and fast food), smoking status, alcohol intake and exercise. The full questionnaire is detailed in ‘Additional file 1’.

